
#### Secondary behavioural outcomes

Secondary behavioural outcomes in the context of the present study are mainly outcomes that we are planning to investigate potential cross-domain far-transfer benefits of the Structure Learning training. These different tasks and key variables of interest are listed in Table 2.

**Table 2 Tab2:** Secondary behavioural tasks and variables of study

Construct/domain	Task	Variables/subtasks
Demographics, Social & Psychological variables	Social questionnaires	• Perceived Stress Scale
		• Pittsburgh Sleep Quality Index
		• Empathy Quotient
		• Social Value Orientation
		• Prisoner’s Dilemma
		• Trust Game
		• Risk Preference
		• Ambiguity Aversion
		• Personal Relative Deprivation Scale
		• Cooperativeness and Competitiveness Personality Scale
		• Tolerance of Uncertainty
		• Multilingualism
		• Perceived Social Support
		• Big Five Inventory
		• Creative Mindset
Language & Numeracy	Woodcock Johnson IV (WJIV)	• Letter-Word Identification
		• Applied Problems
		• Passage Comprehension
		• Calculation
		• Sentence Reading Fluency
		• Maths Facts Fluency
General Intelligence	Raven’s Advanced Progressive Matrices (RAPM)	• Total correct
		• Change in accuracy score
	Wechsler Abbreviated Scale of Intelligence (WASI) Vocabulary	• Total score
	Wechsler Abbreviated Scale of Intelligence (WASI) Block Design	• Total score
Creativity	Verbal Fluency	• Mean fluency score
		• Clustering coefficient
		• Average shortest path length
		• Modularity
	Alternate Uses Task	• Total fluency score
		• Total originality score
		• Total flexibility score
	Remote Associates Test	• Percentage of correct solutions

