### Outcomes {12}

In the present study, multiple behavioural tasks are administered to measure various cognitive constructs. Primary behavioural constructs under investigation include Structure Learning, cognitive flexibility, inhibition, and working memory. Secondary behavioural constructs under investigation include creativity, intelligence, problem-solving, language skills, numeracy skills, social tendencies, and decision making. These measures are conducted only at pre-test assessment, i.e. baseline, only at post-test assessment, i.e. after the end of structure learning training and approximately 2 months from pre-test assessment, or at both pre-test and post-test assessments. Specifically, we administered secondary behavioural constructs measuring language skills, numeracy skills, and intelligence (with the exception of the Raven’s Advanced Progressive Matrices) only at pre-test assessments as they are traits that remain relatively stable across the adult lifespan. We administered primary and secondary behavioural constructs measuring cognitive flexibility (with the exception of the Colour Shape Task), inhibition, working memory, creativity, and problem-solving only at post-test assessments to eliminate possibility of practice effects. Finally, matching tasks, i.e. Colour Shape Task and Raven’s Advanced Progressive Matrices, secondary behavioural constructs that measure social tendencies and decision making (and hence more impervious to practice effects) and all secondary neuroimaging constructs are measured at both pre and post-test assessments. Both the Control and Training groups undergo the same measures at pre and post-test assessments. However, measures for Structure Learning are collected only for the Training group. In addition, we investigate potential neural benefits of the Structure Learning training by assessing secondary neuroimaging outcomes both structurally and functionally. Detailed information regarding the individual tasks used this study can be found in Appendix B in the supplementary information.

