### Sample size {14}

The present study is designed as a scoping study to provide a good estimate of the sample size needed to detect the actual training effect in subsequent studies. Hence, sample size estimation may not be that accurate since the training programme implemented in the current study is novel and effect sizes can be hard to estimate.

Behaviourally, the sample size estimation is based on a statistical power of 0.8 with type I error rate held at an alpha level of 0.05. The estimates of statistical power are all made based on a balanced sample (equal sample size for all conditions) with a 2 × 2 mixed design with one between-subject factors (Group: Control and Training) and one within-subject factor (Time: Pre-test and Post-test). The detection of a Group × Time interaction with a small effect size of *d* = 0.25 and an assumed low population correlation of 0.3 between levels of the within-factor, Time, would need 46 participants for each level in the between-factor, Group.

Sample size estimation is done separately for the different neural measures. In healthy adults, GABA spectral peak height relative to that of water in the PFC generally showed a standard deviation of 0.24. Based on past MRS studies that measure GABA in DLPFC, the detection of a small effect size in GABA spectral peak height relative to water would need 50 participants for each group. In rs-fMRI, based on a reported correlation of *r*= 0.46 between the functional connectivity of corticostriatal networks and performance measures for Structure Learning [33], we derived a sample size of 35 participants per group to detect significant correlations. Finally, as MPM is still a relatively novel scan sequence used to quantify microstructures within the brain, prior data is hence unavailable for us to perform any power computation and sample size estimation. Instead, we sampled published MPM studies that employed similar methodological analyses [52, 53] and opted for an average sample size of 34 participants per group.

Based on sample size computation of the various measures, we opted for the highest sample size of 50 participants per group to ensure sufficient statistical power to detect significant effects in all measures. With a data attrition rate of 20%, the required sample size is set at 60 participants per group.

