## Assignment of interventions: allocation

### Sequence generation {16a}

The allocation sequence is controlled with an algorithm written in R and we employ variance minimisation procedures [55] to match age, sex, intelligence and cognitive flexibility while randomly allocating participants to either the Training or Control group. Intelligence is assessed using the RAPM score, while cognitive flexibility is assessed through the switch cost in accuracy and reaction time on the CST. Both intelligence and cognitive flexibility measures are collected during the Baseline Cognitive Session. The matching algorithm script is executed only when participants within a recruitment batch have all completed the Baseline Cognitive Session. Data from the previous batches of recruited participants is considered during the group allocation. This approach ensures that the two groups remain matched on pre-specified matching variables with each batch of incoming new participants.

Participant data for each matching measure are first collated into a source Excel file. Group assignment for the first recruitment batch is done sequentially upon initialisation of the algorithm. Once the number of assigned participants reaches the number of groups present, i.e. two in the present study, subsequent participants are temporarily assigned to one group at a time. For each potential group assignment, we compute the mean of each matching measure within each group and thereafter derive a mean of means between groups as well as the sum of squared deviations of this group mean. The end goal of the algorithm is to achieve the best minimal sum of squared deviations of this group mean by exploring all possible group allocation of a particular participant. We ensure a balance group allocation of 1:1 (Training vs. Control) by constraining the algorithm such that it will not assign a new participant to the same group as the previous participant.

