Standardised tests used to measure intelligence (RAPM, WASI Vocabulary, WASI Block Design), language, and numeracy skills (WJIV tasks) are widely validated. The RAPM administered in pre-test and post-test are parallel versions that contain items from Set I and Set II of RAPM [56]. The pre-test and post-test versions have Cronbach’s *a*= 0.59 and 0.64 respectively [57]. No concurrent validity was reported during the construction of Zaaiman et al.’s [57] version of RAPM, but items in both versions were selected using empirical data. Only the vocabulary and block design subtests of WASI-II are administered to measure verbal and non-verbal intelligence respectively. Both subtests have excellent internal reliabilities and high concurrent validity, with Cronbach’s *a*ranging from 0.90 to 0.92 and correlation with other intelligence tests ranging from 0.71 to 0.92 [58]. Lastly, the WJIV tasks also exhibit reliability coefficients ranging from 0.74 to 0.97 and have strong concurrent validity with other tests [59].

Preprocessing will first be performed on rs-fMRI data to enhance quality of data. A standard SPM pipeline (http://www.fil.ion.ucl.ac.uk/spm/software/spm12/, SPM12 v7771) will be employed to model fMRI data. We will reslice the aligned EPI data to 2 × 2 × 4 mm^3^ resolution and apply spatial smoothing with a 6-mm isotropic FWHM Gaussian kernel (SPM smooth). The rs-fMRI noises will be processed by standard denoising pipeline in CONN (https://web.conn-toolbox.org, CONN 21a), including linear detrending, 12 potential motion related noise components, noise components from cerebral white matter and cerebrospinal areas, wavelet despiking. Note that the global signal will not be added as a nuisance regressor as suggested by Murphy and Fox [60]. We also correct for inhomogeneity of the magnetic field by acquiring opposite phase encoded field maps (phase encoded direction A-P and P-A). FSL (version 6.0, using topup function) will be used to preprocess the field maps.

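### RAPM is listed as a pre-post change score; compared without baseline adjustment, it is less precise than post-test RAPM adjusted for pre-test RAPM

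*Protocol article*

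**What the plan says.** Under Secondary behavioural outcomes, Table 2 gives RAPM two variables, "Total correct" (no time point stated) and "Change in accuracy score". The text above the table describes its contents as "outcomes that we are planning to investigate potential cross-domain far-transfer benefits of the Structure Learning training".

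Outcomes {12} says that RAPM is measured before and after training, as one of the "matching tasks, i.e. Colour Shape Task and Raven’s Advanced Progressive Matrices". The other intelligence tests, the two WASI subtests, are given at pre-test only.

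Plans for assessment and collection of outcomes {18a} says: "The RAPM administered in pre-test and post-test are parallel versions that contain items from Set I and Set II of RAPM". It reports Cronbach's alphas of "0.59 and 0.64 respectively".

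Sequence generation {16a} makes baseline RAPM a minimisation variable: "Intelligence is assessed using the RAPM score".

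Sample size {14} bases the behavioural calculation on a 2 × 2 mixed design with a Group × Time interaction and an "assumed low population correlation of 0.3 between levels of the within-factor, Time". The article states no model for RAPM itself. Baseline measures appear as covariates only in the model that relates training performance to post-test cognitive flexibility.

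**The concern.** A change score subtracts the baseline with a coefficient of exactly 1. When pre-test and post-test correlate only modestly, that is too much: the error in the baseline passes in full into the outcome. Regression adjustment subtracts only the part of the baseline that predicts the post-test.

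Two features of this trial make the difference matter. The reported alphas are modest, which limits how strongly the two forms can correlate. And the baseline has already been collected and used to balance the groups, so an unadjusted change comparison gives up precision that the design has paid for.

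At stake is the width of the interval for the training effect on the only intelligence test given at both time points. The study also says that it is meant to inform the size of later studies, so a needlessly noisy estimate would carry forward.

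**Working it through.** **Plan's own figure.** The article gives no SD, pre-post correlation or power for RAPM, so there is no RAPM figure to reproduce. Its behavioural figure of 46 per group is not used below; only the r = 0.3 behind it is borrowed.

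**Inputs.** Alphas 0.59 and 0.64, mean 0.615 ({18a}). r = 0.3 as the general behavioural assumption ({14}); values up to 0.6 are an assumed range. n = 50 per group ({14}), or 48 if the planned 60 lose 20% (60 × 0.8). Power 0.80 and alpha 0.05 ({14}), taken as two-sided. Equal pre and post SDs are assumed, with the post-test SD set to 1.

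**Step 1: the model.** With two time points, the Group × Time interaction tests the difference between groups in mean change. It is the two-sample comparison of change scores, with no baseline covariate.

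**Step 2: variances.** Change score: 2(1 − r). Post-test adjusted for baseline: 1 − r². Ratio of adjusted to change: (1 − r²)/[2(1 − r)] = (1 + r)/2, which is below 1 for every r below 1. The raw post-test score has variance 1, so the change score is noisier than ignoring the baseline whenever 2(1 − r) > 1, that is, r < 0.5.

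**Step 3: what the alphas imply.** If the alphas are taken as the reliabilities in this sample, r cannot exceed √(0.59 × 0.64) = 0.614. The reliability of the change score is (0.615 − r)/(1 − r). At r = 0.3 this is 0.315/0.70 = 0.45, so 55% of the variance is error. The error share passes one half at r = (0.615 − 0.5)/0.5 = 0.23.

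**Step 4: detectable difference** in post-test SDs, 2.8016 × √(2 × variance/n), with n = 50. The last column is power for an illustrative difference of 0.5 SD.

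| r | Reliability of change | Variance, change | Variance, adjusted | Ratio | Detectable, change | Detectable, adjusted | Power, change / adjusted |
|---|---|---|---|---|---|---|---|
| 0.3 | 0.45 | 1.40 | 0.91 | 0.65 | 0.663 | 0.535 | 56% / 75% |
| 0.5 | 0.23 | 1.00 | 0.75 | 0.75 | 0.560 | 0.485 | 70% / 82% |
| 0.6 | 0.04 | 0.80 | 0.64 | 0.80 | 0.501 | 0.448 | 80% / 88% |

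With 48 per group at r = 0.3 the detectable differences are 0.677 and 0.546. Put as sample size, at r = 0.3 the adjusted analysis would match 50 per group with 0.65 × 50 = 32.5, about 33 per group.

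**Step 5: unequal SDs.** In general, the change-score variance minus the adjusted variance is (SDpre − r × SDpost)², which is never negative. For r from 0.3 to 0.6 the ratio is 0.78 to 0.94 if SDpre/SDpost = 0.8, and 0.50 to 0.60 if it is 1.25.

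**The case against.** The strongest reply is that Table 2 names variables, not models. Covariates are commonly left to an analysis plan, and none is shown here. If RAPM change is analysed with baseline RAPM as covariate, the group estimate and its standard error equal those of the adjusted post-test score, and the loss disappears. This stands as a condition: the loss applies to the unadjusted comparison. It does not dispose of the point, because the article names a change score, and its only pre-post behavioural model is the unadjusted one.

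A second reply is that minimisation on RAPM should keep the baseline means close, so that the two analyses give nearly the same point estimate. That is fair. The loss then lies mainly in the larger standard error that the unadjusted test attaches to that estimate.

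Four stronger readings are tempting, and the documents do not support them:

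- *The change score is the sole intelligence outcome.* Table 2 also lists total correct, which could be the post-test score.
- *RAPM change is mostly measurement error.* That needs r above 0.23, and RAPM's r is not given. The alphas come from a cited test-construction source and need not hold in this sample.
- *Low reliability makes the outcome unable to show a training effect, so a null result would reflect the instrument.* Reliability of individual change is not sensitivity to a group difference. In the table above, the detectable difference for the change score improves from 0.663 to 0.501 as its reliability falls from 0.45 to 0.04. The article gives no plausible RAPM effect to judge against, and the adjusted score uses the same instrument.
- *The group comparison is biased.* Nothing here shows bias.

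The stakes are also limited. The Objectives section describes the secondary aim as pilot level, and its list of far-transfer domains does not name intelligence.

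**Conclusion.** The point holds as one of precision. An unadjusted comparison of RAPM change, which is what Table 2 and the Group × Time model together describe, is less precise than post-test RAPM adjusted for pre-test RAPM at any pre-post correlation below 1 when the SDs are equal, and never more precise when they differ. At the article's general r = 0.3 the adjusted variance is 35% lower; at r = 0.5 to 0.6 it is 25% to 20% lower. Below r = 0.5 the change score does worse than the raw post-test score.

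These sizes rest on equal SDs, on a correlation that the article does not give for RAPM, and on the analysis being unadjusted. The 55% error share at r = 0.3 rests in addition on the reported alphas applying to this sample. The consequence is a wider interval on one secondary variable.

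**What to change.** In Table 2, specify the between-group RAPM comparison as post-test total correct with pre-test RAPM as covariate. State the time point of the total score at the same place. If the investigators prefer to report change, analyse it with the same covariate; the group estimate is then identical. Baseline RAPM is already a minimisation variable, so adjusting for it also fits the allocation method.

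The cost is one line in Table 2 and one term in the model. No new data or extra testing are needed. If the analysis plan already adjusts for baseline RAPM, the change only brings the article into line with it.

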#### Secondary neuroimaging outcomes

All structural and functional scans are acquired on a 3 T Siemens MAGNETOM Prisma MRI scanner (Siemens Medical Systems, Erlangen, Germany) with a 64-channel head coil. MRI scans were conducted at two timepoints, namely pre-test and post-test for all participants. The same scan sequence is used for all pre-test and post-test MRI scans within each participant. However, there can be changes in scan sequence between participants due to technical issues.(1) Resting-state functional MRI datars-fMRI can reveal functional connectivity within and across brain networks that subserve task performance. A 10-min run of rs-fMRI data is acquired at both pre-test and post-test to investigate functional brain network changes that may result from the Structure Learning training. Before the rs-fMRI scan, participants are instructed to relax, fixate at a white cross presented at the centre of the screen, and to let their mind wander and not think about anything in particular. rs-fMRI images are acquired using Gradient Echo type Echo Planar Imaging (GRE-EPI) sequence with the following parameters: repetition time (TR) = 1280 ms; echo time (TE) = 30 ms; flip angle = 74^◦^; resolution matrix = 220 × 110 × 64; field of view (FOV) = 220 mm; thickness = 2.0 mm; acquisition voxel size = 2 × 2 × 2 mm^3^ resolution; integrated Parallel Acquisition Techniques = 4. A total of 64 slices are used to cover the whole brain including the cerebellum. Each 10-min run results in 462 volumes. In addition, high-resolution T1-weighted structure images are acquired using a Magnetisation Prepared Rapid Acquisition Gradient echo (MPRAGE) sequence with the following parameters: TR = 2000 ms; TE = 2.26 ms; inversion time = 800 ms; flip angle = 8°; FOV = 256 × 256; slices = 176; thickness = 1.0 mm; voxel size = 1 × 1 × 1 mm^3^).(2) Multi-parameter mappingMPM allows us to investigate different aspects of microstructural changes in grey matter and white matter. Recent evidence suggests that myelination is associated with behavioural plasticity in learning [41]. Hence, we focus on MPM parameters sensitive to myelin content, such as R1 and MT. All MPM scans are acquired with a 64-channel radio-frequency (RF) receive head coil and RF body coil for transmission. We use a multi-centre validated MPM protocol [48] in the present study. Three different multi-echo FLASH scans will be acquired with predominant T1-, PD-, and MT-weighting with appropriate choice of the TR and the flip angle. Multiple gradient echoes are acquired with alternating readout polarity at eight equidistant TE between 2.46 and 19.68 ms for the T1w, MTw, and PDw acquisitions. Acquisition parameters for T1-weighting and PD-weighting are as follows: voxel size = 1 × 1 × 1 mm^3^; slices = 176; FOV = 256; resolution matrix = 256 × 256; parallel imaging using GRAPPA factor in the phase-encoding (PE) direction = 2; 6/8 partial Fourier in partition direction, non-selective RF excitation, readout bandwidth BW = 480 Hz/pixel, RF spoiling phase increment = 50°. MT-weighting is achieved by applying an off-resonance Gaussian-shaped RF pulse (4 ms duration, 220° nominal flip angle, 2 k Hz frequency off set from water resonance) prior to the excitation. A pair of RF sensitivity maps are collected before each FLASH scans with the following parameters: 4 mm isotropic resolution, matrix = 256 × 64 × 48, parallel imaging using GRAPPA factor 2 in phase-encoding direction. The total acquisition time is around 15 min. The data-driven approach, i.e. unified segmentation-based correction of R1 maps for RF transmit inhomogeneities (UNICORT), is used to estimate B1 transmit bias field map [49].(3) Magnetic resonance spectroscopyMRS allows for non-invasive in vivo quantification of brain neurometabolites. In the present experiment, we targeted the measurement of the inhibitory neurotransmitter, GABA, in bilateral dorsolateral prefrontal cortex (DLPFC). Prior to all MRS scans, a high-resolution T1-weighted structural scan along the sagittal plane (MPRAGE; TR = 2000 ms; TE = 22.6 ms; TI = 800 ms; flip angle = 8°; FOV = 256 × 256; slices = 176; voxel size = 1 × 1 × 1 mm^3^) is acquired. We then 3D-reconstruct the axial and coronal planes and use images from all three planes to guide our voxel positioning on the DLPFC. We try to achieve consistent MRS voxel placement between subjects and sessions with the use of salient anatomical landmarks such as the dorsal anterior cingulate cortex, superior frontal gyrus, and middle frontal gyrus. In addition, we also try to maximise the sampling of grey matter in each region during voxel placement. After voxel placement, we ensure a homogeneous B_0_magnetic field within the DLPFC voxel with a two-step process. An automated B0 map-based shimming is first used to correct for shifts in linear gradients in the field. Subsequently, an interactive manual shimming procedure is used to correct for residual high-order heterogeneities in the B0 magnetic field. We aim to obtain an eventual shim that is as close to 16 Hz or preferably less than 16 Hz (full-width at half-maximum; FWHM) spectral linewidth. We then measured GABA levels with the widely used technique known as Mescher-Garwood Point Resolved Spectroscopy (MEGA-PRESS) [50, 51]. MEGA-PRESS implements J-difference editing to derive an edited signal that we then use it to quantify GABA levels. Two single voxel edited MR spectra are acquired from a 30 × 15 × 30 mm^3^ (in the *x*, *y*, and *z* dimensions) voxel of interest positioned separately in the left and right DLPFC. Two interleaved datasets are acquired within a single acquisition namely: (1) an edited ‘On’ inversion pulse at 1.98 ppm and (2) an ‘Off’ inversion pulse elsewhere at 7.5 ppm. Additional MEGA-PRESS parameters used are as follows: TR = 2000 ms; TE = 68 ms; spectral bandwidth = 1850 Hz; data points = 2048; readout duration = 1107 ms. We also acquire unsuppressed water spectra as a separate scan to allow for concentration reference to the water tissue. In total, 128 spectral averages (128 ‘On’ and 128 ‘Off’ pulses) are acquired during the metabolite scan and 4 spectral averages are acquired during the water scan resulting in a total scan duration of around 9 min.
